#### The intervention: gANC

The intervention consists of gANC offered at both sites, modified to the needs in each site and group. Women are allocated to a group with women at similar stages of pregnancy within a 4-week gestational age span. From the second visit (gestational weeks 20–26), they receive gANC. Each group will consist of six to eight women and partners (or another support person) for optimal group dynamics and dialogue. While reports of gANC internationally involve numbers in groups of 5–20 in low-income to middle-income countries^41^ and 8–12 in high-income countries,^42^ the need to provide interpreting during groups sessions led to the choice of a somewhat smaller group size as being appropriate to allow all group members a chance to participate in the discussions. Partners are generally encouraged to participate in Swedish ANC, and hence this will be the point of departure also for the gANC but with the final decision about partner participation taken by the women included in each group. Frequency and number of sessions follow the national Swedish programme for antenatal care, that is, eight to nine appointments during a normal pregnancy. Each visit includes a group session for 1 hour, facilitated by one of two midwives assigned to the group and with interpreter assistance. Although each group session has a focus on a theme related to pregnancy, birth or parenting in line with national recommendations,^17^ particular emphasis will be given to issues and questions raised by the participants. Group care allows women to talk with each other and share their experiences in their own language. They also hear midwives’ responses to other women’s questions, expanding the dialogue and information sharing that can occur between midwives and women. The presence of an interpreter facilitates communication between the women and the midwives.

Alongside the group discussion, each woman also has a 15 min individual appointment with the midwife responsible for her care, who is the same midwife for each appointment according to Swedish National Guidelines.^17^ Routine pregnancy controls are carried out, and the woman can also raise any particular issues with her midwife during this time. In total, the time for each visit will be approximately 75 min instead of 30 min, as is common for standard individual care (though this does not take into account the time midwives also spend providing childbirth and parenting classes). Additional individual appointments can be booked as needed if medical or other issues arise. This model for group antenatal care draws on the model used in a previous Swedish study by [name] *et al*
19 24 27 but differs in that two midwives and a language interpreter are present throughout the group sessions, and the principles of PCC and MI are explicitly identified as the theoretical underpinnings for care in the group.

#### Development of evaluation tools

##### Questionnaires

Questionnaires for data collection from participating women were developed by the research team. A number of questions were taken from the Migrant Friendly Maternity Care Questionnaire (MFMCQ),^43^ in some cases slightly modified to fit the purpose of our study, as is the intention in use of the MFMCQ, and for use both in pregnancy and after birth, including occasional changes of tense from the original. Selected questions were also included from the Cambridge Worry Scale (11 single-item questions on worries about the upcoming labour and birth), which is available in English and Swedish,^44^ and the 10-item Edinburgh Postnatal Depression Scale (EPDS) which is available in English, Swedish and Somali.^45^ The questionnaires were developed in English by the research team and translated to Swedish by one of the bilingual team members and then cross-checked by another bilingual researcher in the team. Thereafter, the questionnaire was translated into Somali by a professional Somali translator, fluent in English, Swedish and Somali and finally cross-checked by a Somali-speaking research assistant. At each step of the process, the questionnaire was pilot tested with Somali-born women for relevance and understanding with adjustments made accordingly. During piloting, it was clear that some of the items and response alternatives in the EPDS were difficult for women. Although the scale is translated into Somali, no validation study has to date been published. As data are collected in face-to-face or telephone interviews conducted by the bilingual research assistant, a decision was made to include the EPDS as translated, with the research assistant able to explain the meaning of the questions in plain language if needed. Alongside the current study, we have commenced a process for validating the EPDS Somali translation, involving think-aloud interviews^46^ with Somali-born women to contribute to evidence about the use of the EPDS in Somali.

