##### Outcome measures

Primary outcomes are women’s overall ratings of antenatal care and emotional well-being. Ratings of care are assessed by the core question ‘When thinking about your overall experience of antenatal care—in general, have you been happy with the care that you have received?’ with response alternatives always, mostly, sometimes, rarely and never. The question is modified from MFMCQ^43^ and more detailed questions about specific aspects of care are also included. Emotional well-being is assessed with EPDS, completed in English, Swedish or Somali as appropriate.^45^

Secondary outcomes are adequate number of visits measured by the Adequacy of Prenatal Care Utilization Index, that is, expected number of visits in relation to actual number adjusted for gestational week at booking visit and delivery,^47^ social support during pregnancy using slightly modified questions from the Pregnancy Risk Assessment Monitoring System^48^ and worries about the upcoming birth using questions from the Cambridge Worry Scale.^44^ Knowledge about danger signs and where to seek healthcare if particular symptoms arise are assessed by questions with multiple choice responses, such as ‘Now at the end of your pregnancy, where would you turn if you had bleeding from the vagina? When would you seek care?’. From the patient record, the following are retrieved: estimated time spent with the antenatal care midwife, gestational age at the first ANC visit, lowest measurements of haemoglobin and S-ferritin, weight gain, attendance at parent education, mode of birth, interventions (induction of labour, pain relief including epidural, oxytocin), blood loss, diagnoses (mother) and gestational age, birth weight, Apgar score, umbilical cord pH and the need for neonatal intensive care (infant).

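### The primary EPDS outcome rests on an unvalidated Somali version that the interviewer may explain, and the stated unadjusted comparison of consecutive periods cannot separate a change in delivery from a gANC effect

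*Protocol article*

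**What the plan says.** All references are to the protocol article.

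- **Outcome measures:** "Primary outcomes are women’s overall ratings of antenatal care and emotional well-being". For the second of these, "Emotional well-being is assessed with EPDS, completed in English, Swedish or Somali as appropriate".
- **Development of evaluation tools, Questionnaires:** in piloting "it was clear that some of the items and response alternatives in the EPDS were difficult for women". Of the Somali translation it says that "no validation study has to date been published". Nevertheless "a decision was made to include the EPDS as translated". The remedy for women who have difficulty is help during the interview, "with the research assistant able to explain the meaning of the questions in plain language if needed". The same section adds: "Alongside the current study, we have commenced a process for validating the EPDS Somali translation, involving think-aloud interviews".
- **Design:** controls were recruited from October 2016 to April 2018, and gANC women from May 2018 to December 2019. Data collection ends by July 2020.
- **Participants and recruitment:** the Somali-speaking research assistant is based at site 1, where most recruitment takes place. At site 2 another team member recruits and collects data with the assistant's support.
- **Data collection for the intervention, Questionnaires:** interviews at Q1, Q2 and Q3 are face to face or by telephone, in Somali, Swedish or English.
- **Sample size issues:** the EPDS hypothesis is a fall from 8.0 to 6.0, with 63 women per group. Means are to be compared by t-test, or by Mann-Whitney test if the data are not normal.

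**The concern.** Three features of the plan combine.

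1. In Somali-language interviews, the score depends partly on what the interviewer says when a woman does not follow an item or its response options. Piloting showed that this need is real.
2. The person explaining also takes part in recruitment. Because group is defined by recruitment period, that person knows whether the woman is a control or receives gANC.
3. In a concurrent randomised comparison, gradual change in interviewing would fall on both arms about equally. Here one arm largely precedes the other, so a change in practice would fall unequally on them. So would a change in the share of interviews held in Somali rather than Swedish or English, or by telephone rather than in person.

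The stated test compares two means and has no term for language, mode or interviewer. A shift from any of these sources would be read as part of the gANC effect. At stake is the interpretation of one of the two primary outcomes, and of the EPDS figures that the study is meant to supply for planning later trials.

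**Working it through.** **Implied SD.** The article gives no SD for the EPDS, so 63 per group cannot be strictly reproduced. Solving the usual two-mean formula for the SD, with difference 2.0, n = 63 and 80% power:

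SD = 2.0 × √(63/2) / (z for alpha + z for power) = 11.225 / (z for alpha + 0.842)

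- two-sided 5%: 11.225 / (1.960 + 0.842) = 4.0
- two-sided 20% (the article states an alpha of 20% without saying one- or two-sided): 11.225 / (1.282 + 0.842) = 5.3

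The range 4.0 to 5.3 is used below.

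**Women per group.** 100 expected per group, less 20% loss: 100 × 0.8 = 80.

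**Size of shift (assumed, not from the documents).** Suppose half the women score one or two of the ten items one category differently, all in the same direction, with one category counted as one point. The mean shift between groups is 0.5 × 1 = 0.5 or 0.5 × 2 = 1.0 points. That is 25% or 50% of the hypothesised 2.0.

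**Chance of a significant result with no true effect.** With shift b, SE = SD × √(2/80), and probability = Φ(b/SE − z) + Φ(−b/SE − z).

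| SD | SE | b | b/SE | two-sided 5% | two-sided 20% |
|---|---|---|---|---|---|
| 4.0 | 0.632 | 0.5 | 0.79 | 12% | 33% |
| 4.0 | 0.632 | 1.0 | 1.58 | 35% | 62% |
| 5.3 | 0.838 | 0.5 | 0.60 | 9% | 28% |
| 5.3 | 0.838 | 1.0 | 1.19 | 22% | 47% |

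Without any shift the figures are 5% and 20%. A shift of the same size in the other direction would instead hide a real benefit.

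**How sharply period and group coincide.** The stated dates are recruitment dates, not interview dates. Assume birth at 40 weeks.

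- A control recruited at the end of April 2018 in week 10 reaches week 35 after 25 weeks (late October 2018). She gives birth after 30 weeks (late November 2018) and has Q3 about two months later (late January 2019).
- A gANC woman recruited at the start of May 2018 in week 24 reaches week 35 after 11 weeks (mid-July 2018). She gives birth after 16 weeks (late August 2018) and has Q3 in about late October 2018.

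Late control interviews therefore overlap early gANC interviews at both Q2 and Q3. Most of the control series, which began in October 2016, still comes before any gANC interview. The confounding with time is partial.

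**The case against.** The case on the other side has real weight.

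- **The article may simply be silent.** An interviewer guide could sit in a manual that is not shown, and its absence from an article is no finding. This stands. The text allows explanation only where needed and keeps the translated scale, so a reader who infers that the assistant may explain at will goes beyond it. What remains is the stated rule itself, together with the stated comparison.
- **Continuity.** One full-time bilingual assistant at site 1 appears to serve both periods, and no change of interviewer is reported. This lowers the chance of drift. It does not hold one person's explanations constant over some three years, and it does not cover site 2, where a second team member collects data.
- **The think-aloud work.** A reader might infer that it changes how items are explained from 2018 on. The documents do not say so; its stated purpose is to add evidence on using the EPDS in Somali. It is a possible route for change and no more.
- **Scope.** The English and Swedish versions are also used, and midwives at site 2 reported that most Somali-born families there could communicate in Swedish. The explanation issue is confined to Somali-language interviews. These are probably common at site 1, where many women were not yet fluent in Swedish.
- **The shift is assumed.** This stands. The documents give neither size nor sign.
- **Feasibility purpose and disclosure.** The article discloses the missing validation openly and puts feasibility first. That limits the seriousness of the point, but the EPDS is still named as a primary outcome with a powered hypothesis.

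**Conclusion.** The point holds in a limited form. In Somali-language interviews a primary outcome is collected with a translation that has no published validation, was partly difficult in piloting, and may be explained by someone who knows the study period. Recruitment in consecutive periods and an unadjusted comparison mean that a change in explanation practice, or in the mix of language or mode, would be partly confounded with gANC.

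A reader might go further and infer that the EPDS does drift at the switch to gANC, or that an EPDS difference would be an artefact. The documents support neither: no drift is shown, its direction is unknown, and the interview periods overlap.

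The 9% to 35% range at a two-sided 5% test is an illustration. It rests on an assumed net shift of 0.5 to 1.0 points, 80 women per group and SDs inferred from the sample size. It shows that a shift of a quarter to a half of the hypothesised effect would matter, not that one is expected. The change is worth making because it is cheap and data collection is still open.

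**What to change.** 1. Have the research assistant set down, item by item, the plain-language Somali explanations already in use. Keep to them at both sites, and bring in no change from the think-aloud work until the last Q3 is done.
2. For every remaining interview, record for each EPDS item whether it was explained, plus interview language and mode. Recover language and mode for controls where they were recorded.
3. Report language and mode by period. Report the frequency of explanations descriptively, only for interviews where it was logged.
4. Add an EPDS comparison adjusted for language and mode beside the stated test. It deals with a changed mix of language or mode; it cannot remove a change in the explanations themselves.
5. State in the conclusions that a change in EPDS delivery between periods cannot be excluded.

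An analysis restricted to items that were not explained should not be added. No log of explanations in past control interviews is described. The need for an explanation also depends on comprehension, which gANC is meant to improve, so the restriction would condition on something the intervention may affect.

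**Cost:** a short script, a tick box per item, two recorded fields and one further analysis. Improvements to the Somali explanations wait until data collection ends, and explanation logs will be missing for most controls.

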##### Outcome measures

Primary outcomes are women’s overall ratings of antenatal care and emotional well-being. Ratings of care are assessed by the core question ‘When thinking about your overall experience of antenatal care—in general, have you been happy with the care that you have received?’ with response alternatives always, mostly, sometimes, rarely and never. The question is modified from MFMCQ^43^ and more detailed questions about specific aspects of care are also included. Emotional well-being is assessed with EPDS, completed in English, Swedish or Somali as appropriate.^45^

Secondary outcomes are adequate number of visits measured by the Adequacy of Prenatal Care Utilization Index, that is, expected number of visits in relation to actual number adjusted for gestational week at booking visit and delivery,^47^ social support during pregnancy using slightly modified questions from the Pregnancy Risk Assessment Monitoring System^48^ and worries about the upcoming birth using questions from the Cambridge Worry Scale.^44^ Knowledge about danger signs and where to seek healthcare if particular symptoms arise are assessed by questions with multiple choice responses, such as ‘Now at the end of your pregnancy, where would you turn if you had bleeding from the vagina? When would you seek care?’. From the patient record, the following are retrieved: estimated time spent with the antenatal care midwife, gestational age at the first ANC visit, lowest measurements of haemoglobin and S-ferritin, weight gain, attendance at parent education, mode of birth, interventions (induction of labour, pain relief including epidural, oxytocin), blood loss, diagnoses (mother) and gestational age, birth weight, Apgar score, umbilical cord pH and the need for neonatal intensive care (infant).

#### Preparing for implementation

##### Awareness raising

To create awareness and interest in the project and subsequently in the new model of care, Somali and other community networks are involved in different ways. Information is disseminated by participants in the reference group, by researchers and research assistants one to one and in small groups gathering Somali-born women. A brief pamphlet in Swedish and Somali has been produced and distributed among women, Somali community associations, open playgroups and activity centres and as a poster in the waiting rooms at participating ANC clinics.

##### Training of midwives and interpreters

Areas to be covered in a preparatory training workshop for midwives were identified through findings in the FGDs, in dialogue with the midwives at both sites and in reference group meetings. The research team then tailored a 1 ½ day workshop for all midwives at both sites, held prior to intervention commencement. In response to the needs expressed, the main focus was group processes including PCC^37^ and MI in groups.^39^ A 2-day follow-up session is planned during the intervention period to enable feedback on implementation and address any issues arising.

The interpreters’ preparation included 2 hours of information regarding the structure of the ANC care system, introduction to the Hooyo Project and the gANC model emphasising dialogue and MI principles, participation in meetings with involved midwives and receiving a written project manual (described below).

##### Development of material for midwives leading group sessions

A manual comprising information and suggestions for the content and structure of group sessions has been developed, which the midwives are free to use and adjust according to the needs in the groups. An overview of the availability of evidence-based resources related to pregnancy and birth led us to recommend the use of existing resources where available, as they are free of charge and often in different languages. This also adds to the sustainability and cost-effectiveness of the intervention and makes it easier to duplicate. A study-specific homepage was created, comprising the same information and support as in the written manual.

### Phase III: design and methods for the historically controlled evaluation of the intervention

#### Participants and recruitment

At both sites, primiparous and multiparous Somali-born women are recruited to the study. Recruitment and retention of participants to clinical studies is a well-documented challenge in research across languages and cultures.^49^ We therefore thoroughly planned how to optimise the recruitment and information processes in relation to eligible women and adjusted processes to local prerequisites at both sites. The Somali-speaking research assistant is based at site 1 where most needed and where the majority of the recruitment is performed. In site 2, team member MA is involved with recruitment, information and data collection, supported by the Somali-speaking research assistant form site 1. All pregnant Somali-born women attending the two ANC clinics receive brief information about the study from the midwives during their first visit, and if they agree to receive further information, they are then contacted by the research assistant or MA after the first ANC visit, either by telephone or face to face for further oral and written information in Somali, English or Swedish, as needed.

Inclusion criteria are being born in Somalia and <25 weeks of gestation. Exclusion criterion is a health condition preventing participation in group antenatal care, that is, severe mental health condition or if the pregnancy care were to be transferred to a specialist obstetric clinic. During the first 18 months of the study, recruited women were included in the control group receiving standard individual care, and in the following 18 months, women are included in the intervention group. All women are informed verbally and orally about the purpose of the study and that participation is voluntary. Women included in the control group were informed that their perspectives about their care would contribute knowledge valuable for a proposed intervention study aimed at improving antenatal care for migrant women.

#### Data collection for the intervention

##### Questionnaires

Questionnaire data are collected at three time points (Q1, Q2, Q3). The baseline measurement (Q1) is conducted after recruitment, that is, before gestational week 25. Women are contacted for a face-to-face or telephone structured interview in Somali, Swedish or English at a place of their choice. Q1 includes questions on background (parity, education, income, occupation), migration (time of residence, reason for migration, migration status, language) and social support, psychological and physical well-being, knowledge of danger signs and the health system and expectations about the upcoming birth. Data for Q2 are collected in late pregnancy, after gestational week 35, in the same manner. Q2 includes questions on experiences of care and information during the ongoing pregnancy, knowledge of the health system, pregnancy and birth, social support and psychological and physical well-being and expectations for the upcoming birth. Q3 is administered 2 months postpartum and includes questions regarding the overall experience of pregnancy, ANC, birth and psychological and physical well-being. After each interview, a small gift is offered as a token of appreciation for women’s participation.

##### Medical records

Data for secondary outcome measurement will be collected from patient medical records, for all consenting participants. This includes data related to pregnancy, labour and birth and maternal and infant outcomes.

#### Sample size issues

Our main purpose is to develop and test the feasibility of the intervention and study processes and in so doing, also provide information to inform sample size calculations for possible future randomised controlled trials. Nevertheless, based on available birth rate data, we estimate being able to include 100 women in the control group and 100 women in the intervention group during the study period. We estimate that the study will have the power to detect a clinically relevant increase in women’s overall satisfaction with antenatal care from an expected 65% among Somali women receiving individual care to 82% in those receiving gANC (approximating rates for Swedish speaking women in a national population based study^50^ with 80% power and an alpha of 20%, with 70 women in each group). To have similar power to detect differences in mean scores on the Edinburgh Postnatal Depression Scale (a hypothesised reduction from a mean of 8.0 in the control group— similar to that found in studies of migrant women, to 6.0 in the gANC group—similar to that found in Swedish population-based studies,^51^ 63 women are required in each group. Allowing for 20% loss to follow-up at the time of data collection with women 2 months postpartum, 174 women will need to be recruited.

Differences between groups will be described as ORs and 95% CIs after estimation by means of logistic regression analyses. Comparison of means will be undertaken using t-tests where data are normally distributed or medians compared using Mann-Whitney U tests if not.

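### The 80% power for satisfaction is stated at an alpha of 20%, but the planned 95% CIs correspond to 5%, where power is about 63% at 70, 69% at 80 and 78% at 100 women per group

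*Protocol article*

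**What the plan says.** All of the following comes from the protocol article.

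- **Outcomes.** Under Outcome measures: "Primary outcomes are women’s overall ratings of antenatal care and emotional well-being".
- **Purpose.** Sample size issues opens with feasibility: "Our main purpose is to develop and test the feasibility of the intervention and study processes". It then goes on to make a power claim.
- **Satisfaction.** The effect to be detected is a rise "from an expected 65% among Somali women receiving individual care to 82% in those receiving gANC", "with 80% power and an alpha of 20%, with 70 women in each group". The article does not say whether the alpha is one- or two-sided, and gives no reason for choosing 20%.
- **EPDS.** The sentence begins "To have similar power to detect differences in mean scores on the Edinburgh Postnatal Depression Scale" and arrives at 63 per group for means of 8.0 and 6.0. No standard deviation or separate alpha is given.
- **Recruitment.** "we estimate being able to include 100 women in the control group and 100 women in the intervention group". On attrition: "Allowing for 20% loss to follow-up at the time of data collection with women 2 months postpartum, 174 women will need to be recruited".
- **Analysis.** "Differences between groups will be described as ORs and 95% CIs after estimation by means of logistic regression analyses". The article mentions no 80% interval, one-sided test or 20% significance threshold.

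**The concern.** A power figure is useful only if it refers to the analysis that will be presented. Here the sizing uses one error rate and the reporting another, and the article does not connect them. A reader who sees 80% power and then a 95% interval will take the two to belong together.

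If the hypothesised 17-point gain is real, that reader expects the interval to include no effect about one time in five. The true risk is higher. An interval that includes an odds ratio of 1 could then be taken as evidence that group care made no difference, when the study was less able to show one than its plan suggests. Satisfaction is a primary outcome, and the Discussion says the study will indicate whether group care improves women's experiences, so the interval is likely to be read this way. The study is also meant to inform the sample size of later randomised trials, and an unclear error rate could be carried into them.

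**Working it through.** **Inputs** (Sample size issues): p1 = 0.65, p2 = 0.82, so d = 0.17 and the mean proportion is 0.735; equal groups; target power 80% (z = 0.8416); design alpha 20%; reporting level 95% CI, which means two-sided alpha 5%.

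**Formulas** (two proportions, pooled variance under the null)

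- A = √(2 × 0.735 × 0.265) = 0.6241
- B = √(0.65 × 0.35 + 0.82 × 0.18) = √0.3751 = 0.6125
- n per group = (z_α·A + 0.8416·B)² / d²
- power = Φ[(d√n − z_α·A) / B]; with continuity correction, replace d by d − 1/n

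**Step 1. Reproduce the plan's figure at two-sided 20% (z_α = 1.2816).**

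- n = (0.7999 + 0.5155)² / 0.0289 = 59.9, so 60 per group. With continuity correction it is 71.1, so 72.
- Power at 70 per group: (1.4223 − 0.7999) / 0.6125 = 1.016, giving 84.5%. With continuity correction 79.4%; with Fisher's exact test 80.3%.

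The stated 70 is therefore a sound figure for a two-sided 20% alpha with a continuity-corrected or exact method. Two-sided 20% is numerically the same as one-sided 10%. A one-sided 20% alpha would need only 38 (49 corrected).

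**Step 2. Could 20% be a misprint for 5%?** At two-sided 5%, n is 105 (117 corrected; 102 with unpooled variance; 104 by the arcsine method, 103.3 before rounding up). At one-sided 5%, n is 83 (94 corrected). None of these is near 70, so the calculation did use an alpha of about 20%.

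**Step 3. Power at the level of the planned interval (two-sided 5%, z_α = 1.960, z_α·A = 1.2233).**

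| Analysed per group | Source of the number | (d√n − 1.2233)/B | Power | With continuity correction |
|---|---|---|---|---|
| 70 | stated requirement | (1.4223 − 1.2233)/0.6125 = 0.325 | 62.7% | 55.2% |
| 80 | 100 recruited × 0.8 | (1.5205 − 1.2233)/0.6125 = 0.485 | 68.6% | 61.9% |
| 100 | 100 recruited, no loss | (1.7000 − 1.2233)/0.6125 = 0.778 | 78.2% | 73.1% |

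Other methods at 70 per group agree: exact chi-square 63.7%, arcsine 63.5%, Wald test on the log odds ratio 61.3%, Fisher's exact test 55.6%. The last two matter most, since the first is closest to the planned logistic regression and the second to the method that reproduces 70.

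The chance that the 95% interval includes no effect when the assumed gain is real is thus about 37% at 70, 31% at 80 and 22% at 100 per group.

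**Step 4. Detectable difference at 70 per group, 80% power, two-sided 5%.** With a control rate of 65%, an intervention rate of 85% gives 78.6% power and 86% gives 83.1%. The detectable contrast is about 65% vs 85–86%.

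**Step 5. EPDS.** Solving n = 2·SD²·(z_α + 0.8416)² / 2² for n = 63 gives SD = 2√31.5 / (z_α + 0.8416). That is 4.0 at two-sided 5% and 5.3 at two-sided 20%. Both are back-calculated assumptions, because the article gives no SD.

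**The case against.** The strongest defence is that the article is open about its alpha and correct at it. A reader might infer that the 80% is a calculation error; Step 1 shows that it is not. The fault lies in the link between sizing and reporting.

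Second, a reader might infer that the trial will be declared positive or negative at 5%. The article says only that differences will be described with 95% intervals and gives no decision rule, and feasibility is the main purpose. A relaxed alpha can be defended in such a study, and a descriptive 95% interval does not strictly contradict it. This lowers the severity. It does not remove the mismatch, because the power claim is explicit and 95% is the only level at which results will be shown.

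Third, 70 is the calculated requirement, while 100 per group are expected. The 20% loss is tied to the interview 2 months postpartum, whereas experiences of care are also asked about in late pregnancy, and Outcome measures does not fix the time point for satisfaction. More than 80 per group may therefore be analysed. This stands, which is why the result is given for 70, 80 and 100. Even at 100 the figure is just under 80%.

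Three further inferences are tempting but unsupported:

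- **That the two primary outcomes were sized at different alphas.** The EPDS figure fits 20% with an SD of 5.3 as well as it fits 5% with an SD of 4.0. The SD may stand in the full protocol, which is not shown.
- **That an alpha of 20% on both outcomes inflates the chance of a false positive to a specific value.** That would need a 20% decision rule, which is not stated, and an assumption about how the outcomes are correlated.
- **That the total of 174 is wrong.** 140/0.8 = 175, and equal groups would need 88 each, or 176. The gap is rounding and has no consequence with 200 women expected.

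**Conclusion.** The point holds as a mismatch between the design alpha and the reporting level. The stated 80% is right at a two-sided 20% alpha. At the two-sided 5% level of the planned 95% intervals, power for 65% vs 82% is about 63% at 70 per group, 69% at 80 and 78% at 100, and lower with a continuity-corrected or exact method (55–56% at 70).

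This rests on the article's own rates, equal groups, an unadjusted comparison, and the usual equivalence between a 95% interval and a two-sided 5% test. The EPDS sizing is an open question and not a demonstrated inconsistency.

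It should be fixed, because it concerns the stated power for a primary outcome. It does not undermine the study's feasibility aims.

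**What to change.** Use one alpha for both sizing and reporting, and state whether it is one- or two-sided. There are two ways to do this:

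1. **Keep the 95% intervals.** Restate power for satisfaction as about 63% at 70, 69% at 80 and 78% at 100 women per group, or restate the difference detectable with 80% power at 70 per group as about 65% vs 85–86%.
2. **Keep the 20% level.** Say that it is a screening level chosen for a feasibility study, report 80% intervals beside the 95% intervals, and label the comparison non-confirmatory.

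In either case, confirm that the 63 per group for the EPDS rests on the same alpha, and give the SD that was used.

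The cost is the rewording of one section and, under the first option, a less favourable stated power. Neither option needs more women or any change to recruitment.
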